### Subgroup Analyses

3.4

Prespecified subgroup analyses will be performed for the following variables:
Age (higher or lower than median).Sex (male vs. female).Initial rhythm (shockable vs. non‐shockable).Time to ROSC (higher or lower than median).Witnessed arrest (yes vs. no).Bystander cardiopulmonary resuscitation (yes vs. no).Presence of ST‐segment elevation myocardial infarction on admission (yes vs. no).Lactate level on admission (higher or lower than median).

Subgroup analyses will be performed using regression‐based tests for interaction. Results will be interpreted cautiously, given the risk of type I error with multiple comparisons. No formal adjustment for multiplicity will be applied, but findings will be clearly labeled as exploratory.

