### Sample Size

2.6

The trial aims to include 1000 patients across five sites, covering the entire Danish population. Sample size calculations were performed separately for each intervention based on its primary outcome.

For the Dexamethasone and backrest elevation interventions (primary outcome: 90‐day mortality), assuming an overall mortality of 35% and a 25% relative risk reduction (to 26% mortality), with 85% power and a two‐sided significance level of 5%, 468 patients per group are required. To account for potential dropouts and loss to follow‐up, 500 patients per group (1000 total) are planned.

For the olanzapine and early wakeup interventions (primary outcome: days alive outside hospital within 30 days), estimates assumed 35% mortality during initial hospitalization (0 days alive outside hospital) and a mean of 15 days outside hospital for survivors, yielding a population mean of 9.8 days with an estimated standard deviation of 7 days. To detect an increase of 1.5 hospital‐free days with > 90% power and a two‐sided significance level of 5%, a total of 920 patients were required.

The combined sample size of 1000 patients provides adequate power for all four primary outcomes within the factorial design. The trial is not powered to detect interactions between interventions; prespecified interaction analyses (Section 3.5) are exploratory and hypothesis‐generating.

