#### Mortality Outcomes (Dexamethasone and Backrest Interventions)

3.2.1

The primary analysis for the Dexamethasone and elevated backrest interventions will use log‐binomial regression to estimate the relative risk of 90‐day mortality, defined as the proportion of patients who die from any cause between randomization and day 90. This will also be reported for the early wake‐up and olanzapine interventions. If log‐binomial models are infeasible due to non‐convergence, logistic regression models will be used instead, and OR will be reported instead of RR. As additional analyses, Kaplan–Meier curves for each allocation group will be estimated, graphically displayed, and compared by the log‐rank test. Furthermore, Cox proportional hazards models will be applied to estimate hazard ratios with 95% confidence intervals for time to death between treatment groups as a secondary outcome for all four interventions. As prespecified subgroup analyses, the interaction between treatment allocation and each of the following baseline variables will be assessed: sex, age, time to ROSC, lactate level upon hospital admission, shockable primary rhythm, witnessed cardiac arrest, bystander‐performed CPR, and presence of STEMI consistent with acute myocardial infarction. Proportional hazards assumptions will be assessed using Schoenfeld residuals and log–log plots. If deviations from the proportional hazards assumption are detected, the relevant covariates will be included with time‐varying HR instead, or if this is not sufficient to solve the deviation, Cox regressions with stratified baseline hazards will be utilized. Further, causes of death (cardiovascular, neurological, multi‐organ failure) between the treatment arms will be compared as competing risks with the Nelson‐Aalen cumulative incidence method as hypothesis generating. Any changes from the pre‐specified analysis plan will be reported.

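### Section 3.4 tests effect modification by age, time to ROSC and lactate only after a split at the trial's own median; this is valid, but it costs about a third of the information if modification is roughly linear

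*SAP article*

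**What the plan says.** Section 3.4 (Subgroup Analyses) lists eight baseline variables. Five are naturally binary. The other three are continuous and are cut in two: "Age (higher or lower than median", "Time to ROSC (higher or lower than median" and "Lactate level on admission (higher or lower than median". The analyses are to be "performed using regression‐based tests for interaction". There is no multiplicity adjustment, and "findings will be clearly labeled as exploratory". No numeric or clinical threshold is given, so the cut can only be the median of the patients in this trial. No linear, transformed or spline analysis of the three variables appears anywhere in the article.

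Section 3.2.1, on the mortality outcomes, also prespecifies interactions between treatment and baseline variables, naming "sex, age, time to ROSC, lactate level upon hospital admission" among them. It does not say whether the continuous ones enter as measured or split.

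**The concern.** A median split treats a value just above the middle the same as an extreme one. If the treatment effect varies gradually with age, time to ROSC or lactate, the split discards the part of each variable that carries most of the signal. The cut value is also unknown until the data are in and will differ from trial to trial.

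What is at stake is the chance of detecting gradual effect modification in tests that the trial was not sized for. Section 2.6 bases the sample size on main effects only. Because 3.2.1 gives no scale, the reader must also infer that 3.4 governs the mortality interactions.

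**Working it through.** **Inputs from the SAP article.** Section 2.6: "The trial aims to include 1000 patients across five sites", so about 500 per level of each factor; mortality 35% against 26%; 85% power; 468 per group. Section 3.1: two-sided tests at 5%. Section 3.4: the three median splits.

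**The plan's own figures.** The article gives no figure for the subgroup tests, so only the main-effect sample sizes can be checked. With pooled variance, n per group = [1.960·√(2·0.305·0.695) + 1.036·√(0.35·0.65 + 0.26·0.74)]² / 0.09² ≈ 468.4. That is 469 rounded up, against 468 stated. For days alive outside hospital (1.5 days, SD 7, 90% power) the total is 916 against 920 stated. Both reproduce.

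**Information kept by a median split.** For a modifier X and an interaction linear in X, the efficiency of the split relative to the continuous test is the squared correlation between X and the indicator that X exceeds its median. For a normal X this is 2/π = 0.637, a loss of 1 − 0.637 = 36.3%. The equivalent sample size is 1000 × 0.637 ≈ 637.

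The documents give no distribution for these variables, so the shape is an assumption. Values below are on the scale on which the interaction is taken as linear:

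| Assumed shape | Kept | Lost |
|---|---|---|
| Uniform | 75% | 25% |
| Normal (or normal after a log transformation) | 64% | 36% |
| Lognormal, log-SD 0.4 | 56% | 44% |
| Exponential | 48% | 52% |
| Lognormal, log-SD 0.7 | 42% | 58% |

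**Effect on power, normal case.** The expected test statistic shrinks by √0.637 = 0.798.
- 80% power on the continuous scale: (1.960 + 0.842) × 0.798 = 2.236, and Φ(2.236 − 1.960) ≈ 61%.
- 90% power: (1.960 + 1.282) × 0.798 = 2.586, and Φ(2.586 − 1.960) ≈ 73%.

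**Simulation check.** 1000 patients, 1500 replicates per setting, normal modifier x, treatment t, logit of death = −0.7 + 0.6x − 0.3t + b·t·x, Wald test of the interaction. All coefficients are assumptions. At x = 0 they imply risks of 33% and 27%. The model is logistic, which is the fallback for log-binomial regression in 3.2.1.

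| b per SD | Power, continuous | Power, median split |
|---|---|---|
| 0 (type I error) | 5.1% | 4.3% |
| 0.30 | 47% | 31% |
| 0.45 | 78% | 58% |
| 0.50 | 86% | 66% |

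These agree with the 0.798 scaling: from 78.3%, (1.960 + 0.783) × 0.798 = 2.189, and Φ(0.229) ≈ 59%.

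**The opposite case.** When the true modification was a step at the median (0.9 on the log-odds scale), the split had 86% power and the continuous test 71%.

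**The case against.** The strongest reply is that nothing is broken. The split is prespecified and made on a baseline variable without reference to outcome. Type I error is held, interaction tests are used rather than separate within-subgroup p-values, and the results are labelled exploratory. All of that stands, and it limits the point to an improvement in method.

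The assumed interactions are also large. The plan's own mortality effect is a log odds ratio of ln(0.35/0.65) − ln(0.26/0.74) = 0.43, so slopes of 0.30 to 0.50 per SD are about 70% to 117% of it. Halving the smallest slope to 0.15 halves the expected statistics implied by 47% and 31% power, giving about 15% power against 11%. With modification that weak, neither test is informative and little is recovered. This stands too.

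Some stronger readings are tempting but are not supported:
- A reader might infer that 3.2.1 and 3.4 contradict each other. Section 3.2.1 is silent on scale and 3.4 supplies the form; the two are compatible, and only a cross-reference is lacking.
- A reader might infer that a sample median is a cut-off tuned to the results. It is fixed in advance by rule and does not depend on outcomes.
- A reader might infer that patients exactly at the median would be lost, or that there will be many. The wording is ordinary shorthand, the article gives no figures on ties, and a condensed article may leave the rule to the full plan or the code.
- A reader might infer that the results could not be pooled or used elsewhere. The median can be reported and the measured values are kept.
- A reader might infer that severity of the arrest is the likeliest modifier. Section 3.4 does not rank its eight variables.

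**Conclusion.** The point holds as a low-cost improvement to an exploratory analysis. Section 3.4 fixes a less sensitive test than the same data allow, provided modification is roughly linear. The loss is then about 36% of the information for a near-normal or log-transformed modifier, and about 25% to 58% over the shapes assumed here. In power terms, 80% becomes about 61% and 90% about 73%.

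The loss is not unconditional. It rests on a linear interaction and on an assumed covariate distribution, neither of which the article states. It vanishes, and the ranking reverses, if the true modification is a step at the median; the plan gives no reason to expect such a step. No primary analysis and no sample size changes.

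**What to change.** In section 3.4, prespecify the interaction test with age, time to ROSC and admission lactate as continuous variables in the same regression models. Use the log scale for lactate and time to ROSC if they are skewed, and a restricted cubic spline as a check on shape. Fix the transformation and the number of knots in advance, so that the change does not add analytic freedom. Keep the median split as a descriptive forest-plot row, report the median value beside it, and assign values equal to the median to the lower group. In section 3.2.1, add a reference to 3.4 for the form of these variables.

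The cost is a few sentences and slightly more programming, with no new data, and the planned median-split display is retained. The downside is that a linear term assumes a shape, which the spline is there to check.

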### Assessment of Interactions Between Interventions

3.5

As a safety measure and to investigate potential synergistic or antagonistic effects, interactions among the four interventions will be assessed with respect to 90‐day mortality, days alive outside the hospital within 30 days, and the occurrence of serious adverse events. Interaction terms will be included in regression models, and interactions will be considered significant if the interaction term has *p* < 0.01 and demonstrates a clinically important effect (based on the anticipated intervention effect used in sample size calculations, i.e., absolute risk reduction of 5.6%).

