All statistical significance tests will be two‐sided, with a significance level of 5%. No alpha spending or adjustment of the final significance level is required, as the planned interim analysis at 500 enrolled patients is a safety review conducted by the independent data‐monitoring committee without formal efficacy or futility testing (see Section 3.9). Throughout, categorical variables will be presented as counts with proportions, whereas continuous variables will be presented as means ± standard deviations for normally distributed variables or medians (25th–75th percentiles) for nonnormally distributed variables. The normal distribution will be evaluated using quantile‐quantile plots.

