### Safety Analyses

3.8

Adverse events and serious adverse events will be summarized by intervention group using descriptive statistics. The following adverse events will be specifically monitored: major bleeding, infections (pneumonia, sepsis, pyelonephritis, upper airway infections), renal impairment requiring renal replacement therapy, electrolyte disorders, metabolic disorders (hypoglycemia, prolonged hyperglycemia), cardiac events (ventricular fibrillation, ventricular tachycardia, atrial fibrillation requiring cardioversion, new need for pacing, prolonged QT interval > 560 ms, circulatory collapse), respiratory events (auto‐extubation, need for reintubation), seizures (tonic–clonic, myoclonic, status epilepticus), extrapyramidal side effects, skin complications (pressure ulcers, acne, atrophy, purpura, reduced wound healing), and death after withdrawal of life‐sustaining therapy.

Adverse reactions potentially related to specific interventions will be identified:
Dexamethasone: Infections, hyperglycemia, skin complications (acne, atrophy, purpura, reduced wound healing).Olanzapine: Ventricular arrhythmias, prolonged QT interval, bucco‐linguo‐masticatory syndrome.Backrest elevation: Pressure ulcers occurring within 96 h.

Safety outcomes will be analyzed using descriptive statistics and risk ratios with 95% confidence intervals. No formal hypothesis testing will be performed for safety outcomes, but clinically meaningful differences will be highlighted.

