### Methodologic Considerations

4.4

The factorial design requires careful attention to potential interactions. If interventions act through independent mechanisms without synergy or antagonism, factorial analysis is efficient and valid. However, if substantial interactions exist, main effects may be misleading. This plan includes rigorous assessment of interactions, with criteria for both statistical significance (*p* < 0.01) and clinical importance (absolute effect ≥ 5.6%) to avoid false‐positive findings. If important interactions are identified, results will be presented with appropriate stratification.

The modified intention‐to‐treat approach balances statistical rigor with clinical pragmatism. Including only participants who meet the inclusion criteria avoids diluting treatment effects from ineligible patients while maintaining randomization integrity. Per‐protocol analyses will provide complementary information about intervention effects under ideal adherence but must be interpreted cautiously given potential selection bias.

Handling of missing data follows current best practices. Registry linkage for mortality ensures complete ascertainment of the primary outcome for Dexamethasone and backrest interventions. Days alive outside the hospital can be ascertained from hospital records and national registries with minimal missingness. Nevertheless, the plan includes multiple imputation and sensitivity analyses to assess the robustness of the findings under different missing‐data assumptions.

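### Section 3.5 puts serious-adverse-event interactions behind a p < 0.01 gate, although Section 3.8 bars tests of safety outcomes and a safety screen needs sensitivity

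*SAP article*

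**What the plan says.** Section 3.5 of the SAP article gives the interaction analysis two purposes: "As a safety measure and to investigate potential synergistic or antagonistic effects, interactions among the four interventions will be assessed". The endpoints are 90-day mortality, "days alive outside the hospital within 30 days, and the occurrence of serious adverse events". One decision rule covers all three: "interactions will be considered significant if the interaction term has" p < 0.01 and, in addition, the effect is clinically important, "based on the anticipated intervention effect used in sample size calculations, i.e., absolute risk reduction of 5.6" per cent. The section refers only to regression models and names no effect scale.

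Section 3.8 sets the rule for safety outcomes: descriptive summaries by intervention group and risk ratios with 95% confidence intervals. It adds: "No formal hypothesis testing will be performed for safety outcomes, but clinically meaningful differences will be highlighted". It makes no exception for interactions and does not refer to Section 3.5.

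Three other places bear on the point.
- Section 4.4 says the two-part criterion is there "to avoid false‐positive findings".
- Sections 3.1 and 4.4 provide stratified results when an important interaction has been identified.
- Section 2.6 states that the trial lacks power for interactions and treats these analyses as exploratory.

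**The concern.** Serious adverse events come under both sections, and the two rules differ. An analyst following Section 3.5 tests the interaction at 1%; an analyst following Section 3.8 tests nothing and reports estimates with intervals.

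The direction of the gate is the second problem. The general level in Section 3.1 is "All statistical significance tests will be two‐sided, with a significance level of 5" per cent. Section 3.5 is stricter, for the reason given in Section 4.4. That reason fits a claim that two interventions work better or worse together. A safety screen has the opposite priority, because overlooking a harmful combination costs more than following up a chance finding.

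All patients are co-randomised to four interventions, so harm from a combination is a risk specific to this design. The only stated route to results by combination is an interaction that passes the gate. Otherwise serious adverse events are summarised by single intervention, and nothing commits the plan to showing event risks in the combination cells.

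**Working it through.** **Inputs from the plan.** "The trial aims to include 1000 patients across five sites" (Section 2.6); 1:1 allocation to each intervention (Section 2.3); p < 0.01 and 5.6 points (Section 3.5); two-sided tests (Section 3.1).

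**Assumed.** The plan gives neither a serious-adverse-event rate nor a scale. I use rates from 5% to 50% and the risk-difference scale, on which the 5.6-point criterion is expressed.

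**The plan's own figures.** The plan states no detectable interaction, so only its sample sizes can be reproduced.
- Mortality of 35% against 26%, two-sided 5%, 85% power: (1.960 + 1.036)² × (0.35 × 0.65 + 0.26 × 0.74) / 0.09² ≈ 466 per group. The pooled-variance version gives 469. The plan states 468.
- A difference of 1.5 days with SD 7 and 90% power gives 916 in total. The plan states 920.

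These agree, so I take N = 1000 as given.

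**Pairwise interaction.** Any two interventions form a 2 × 2 table with 1000 / 4 = 250 patients per cell. The interaction is the difference between two risk differences. With a common event rate p,

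SE = sqrt(4p(1 − p) / 250).

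The smallest observed interaction with two-sided p < 0.01 is 2.576 × SE. At p < 0.05 it is 1.960 × SE, which is also the half-width of a 95% interval. The true size needed for 80% power at the 1% level is (2.576 + 0.842) × SE. For example, at 20%: SE = sqrt(0.64 / 250) = 5.06 points, and 2.576 × 5.06 = 13.0 points.

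| Assumed event rate | SE (points) | Observed size needed, p < 0.01 | Observed size needed, p < 0.05 | True size for 80% power at 0.01 | Power at 0.01 for a true 5.6 points |
|---|---|---|---|---|---|
| 5% | 2.76 | 7.1 | 5.4 | 9.4 | 29% |
| 10% | 3.79 | 9.8 | 7.4 | 13.0 | 14% |
| 20% | 5.06 | 13.0 | 9.9 | 17.3 | 7% |
| 35% | 6.03 | 15.5 | 11.8 | 20.6 | 5% |
| 50% | 6.32 | 16.3 | 12.4 | 21.6 | 5% |

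A true interaction of 10 points would reach p < 0.01 in 27%, 18% and 16% of trials at rates of 20%, 35% and 50%.

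**Which condition decides.** The 5.6-point condition is the stricter one only if 2.576 × SE < 5.6, that is SE < 2.17 points, so p(1 − p) < 0.0217² × 250 / 4 ≈ 0.0295 and p is about 3% or lower. Above that rate the p-value decides. (Section 2.6 uses 35% to 26%, a difference of 9 points. Where 5.6 comes from is a separate question; I take it as written.)

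**Sensitivity to scale.** Suppose only the cell receiving both interventions has a raised risk, over base rates of 5% to 50%. The excess needed for p < 0.01 is 8.3 to 16.1 points on the risk-difference scale, 12.1 to 16.5 on log-odds and 13.0 to 18.0 on log-risk. A ratio scale therefore does not make the gate more sensitive at low rates.

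**Higher order.** For a three-way interaction the SE doubles, and the threshold is about 26 to 33 points at rates of 20% to 50%.

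**The case against.** The strongest reply is that sample size, not the 1% level, causes most of the insensitivity, and that the plan says so. At rates of 20%, 35% and 50% an ordinary 5% test would still need 9.9, 11.8 and 12.4 points, so the stricter level adds only about 3 to 4 points. This stands: the change proposed here improves what is shown and does little for detection.

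The 1% level also has a rationale. Four interventions give 6 + 4 + 1 = 11 interaction terms, and three endpoints make up to 33 tests. By chance alone one expects 33 × 0.05 ≈ 1.7 signals at 5% and 33 × 0.01 ≈ 0.3 at 1%. That is a fair reason for a strict rule on claims of interaction. It does not favour a pass/fail rule where estimates with intervals would serve.

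Section 3.5 can be read as a specific rule beside the general one in Section 3.8. Since neither section refers to the other and Section 3.8 has no exception, the text does not settle this.

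Two stronger readings are tempting.
- A reader might infer that an interaction missing the gate is declared absent. The documents do not say so. Section 3.5 says only when one is considered significant, Section 2.6 labels the analyses exploratory, and Sections 4.2 and 4.4 warn that interactions could complicate or mislead. Section 3.8 also allows notable differences to be highlighted and Section 3.12 promises estimates with intervals, although neither names combinations.
- A reader might infer that no combination harm below 13 to 16 points could ever be flagged. That range holds only for assumed rates of about 20 to 50% on the risk-difference scale. It is a threshold for the observed effect: a true effect of that size passes about half the time, and a smaller one passes sometimes.

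**Conclusion.** The point holds as an inconsistency together with a poorly suited rule. Sections 3.5 and 3.8 cannot both be followed for serious adverse events, and a gate designed against false positives is the wrong instrument for a safety screen. Its size depends on the event rate: at least about 7 to 10 points observed at 5 to 10%, and 13 to 16 points at 20 to 50%, with 250 patients per cell on the risk-difference scale. Throughout that range the p-value decides, and an interaction of the 5.6 points that the plan calls clinically important would pass in about 5% to 29% of trials. The practical consequence is limited to reporting: event risks by combination are assured only if the gate is passed. The primary analyses are unaffected. The point should be corrected, but it does not threaten the trial's main conclusions.

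**What to change.** In Section 3.5, take serious adverse events out of the p < 0.01 rule. For each of the six pairs of interventions, report the event risk in each of the four cells and the interaction as a risk difference with its 95% confidence interval, whatever its significance. Label these results exploratory, and state that a wide interval is not evidence of no interaction. In Section 3.8, add a cross-reference so that both sections follow one estimation-only rule.

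Keep a single rule for 90-day mortality and days alive outside hospital, and report their interaction estimates with 95% intervals as well. Mortality should not be split into a safety reading and an efficacy reading, since that would place one estimate under two rules.

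The cost is a few sentences and six small tables from data already being collected. The downside is that some chance imbalances will be displayed: with six intervals, 6 × 0.05 = 0.3 would be expected to exclude zero by chance. At event rates of 20 to 50% the intervals will have half-widths of about 10 to 12 points, so the tables will show the uncertainty and will not remove it.

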### General Principles

3.1

All analyses will be conducted according to the modified intention‐to‐treat principle, including all randomized participants who meet the inclusion criteria and have available outcome data, or imputed outcome data (see missing data section below). Participants who do not fulfill the inclusion criteria will be excluded from analyses. If consent is subsequently withdrawn, data collected prior to withdrawal will be included in the primary analysis in accordance with the EU Clinical Trials Regulations, unless the participant explicitly requests deletion of their data. A per‐protocol analysis will be performed as a sensitivity analysis, including only participants who received all scheduled doses of pharmacologic interventions, adhered to the assigned backrest position for ≥ 80% of the time, and had a wakeup call attempted within the assigned time frames.

Data will be analyzed and reported as four individual trials, with no adjustment for multiple comparisons planned. This approach is justified because almost all previous trials in the hospital phase of out‐of‐hospital cardiac arrest care have been neutral, and all four interventions are accepted without considering potential interactions. If more than one intervention shows a non‐neutral result, interactions between interventions will be evaluated by including pairwise and higher‐order interaction terms in the primary regression models for each intervention, applying the prespecified thresholds defined in Section 3.5 (interaction *p* < 0.01 and absolute effect ≥ 5.6%). If a clinically important interaction is identified, results for the affected interventions will be presented both as overall estimates and stratified by the interacting intervention allocation. All regression analyses will be adjusted for site as a covariate.

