### Limitations

4.2

Several limitations warrant consideration. The analysis plan does not adjust for multiple comparisons across the four interventions, increasing the risk of Type I error. This decision reflects the pragmatic consideration that all four interventions address distinct mechanistic pathways and are justified independently. However, findings will be interpreted cautiously, and interactions will be evaluated if multiple interventions show non‐neutral results. Second, the factorial design assumes no interactions between interventions. While preliminary simulations suggest adequate power even with minor interactions, substantial interactions could reduce power and complicate interpretation. Third, the backrest elevation and early wakeup interventions are unblinded, potentially introducing performance and detection biases. However, primary outcomes (mortality and days alive outside the hospital) are objective and ascertained by blinded assessors. Fourth, the per‐protocol analysis may be affected by selection bias if nonadherence is related to prognosis. Results will be interpreted as exploratory and hypothesis‐generating. Fifth, anticipated intervention effects informing sample size calculations are based on clinical judgment and prior trials, introducing uncertainty. Statistical power may be lower if true effects are smaller.

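### The 5.6% interaction cutoff is not the sample-size effect it is said to be and cannot be applied to days alive outside hospital; the SAP also disagrees with itself on whether interaction checks depend on the main results

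*SAP article*

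**What the plan says.** **The cutoff.** Section 3.5 assesses interactions for three outcomes: 90-day mortality, days alive outside hospital within 30 days, and serious adverse events. An interaction counts if p < 0.01 and the effect is clinically important. The size criterion is "based on the anticipated intervention effect used in sample size calculations, i.e., absolute risk reduction of 5.6" per cent. Section 3.1 repeats the 5.6% figure, and Section 4.4 describes it as the criterion for "clinical importance (absolute effect ≥ 5.6%) to avoid false‐positive findings".

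**The planning effects.** Section 2.6 plans the dexamethasone and backrest comparisons by "assuming an overall mortality of 35% and a 25% relative risk reduction (to 26% mortality"). The olanzapine and early wakeup comparisons are planned on a gain of 1.5 days with an SD of 7. The figure 5.6 does not appear there.

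**When interactions are examined.** Section 3.1: "If more than one intervention shows a non‐neutral result, interactions between interventions will be evaluated". Section 4.2 says that "interactions will be evaluated if multiple interventions show non‐neutral results". Section 3.5 attaches no condition: it presents the assessment as a safety check and as a search for synergy or antagonism.

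**The models.** Section 3.1 adds interaction terms to the primary regression model of each intervention. For mortality that model is log-binomial, with logistic as fallback (Section 3.2.1). For days the primary analysis is a Wilcoxon rank-sum test; a mixed-effects linear regression appears only as a sensitivity analysis (Section 3.2.2).

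**The concern.** Under Sections 3.1 and 4.4 this rule decides whether results are shown stratified by the interacting intervention or only as overall estimates. Three things about it look wrong.

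- The threshold is attributed to a calculation that used another number.
- One absolute-risk figure is set for outcomes and model terms to which it does not directly apply. For days, no cutoff is stated on the outcome's own scale, and no primary regression model exists to carry the interaction term.
- Two sections make the check depend on the main results and one does not. A factorial trial relies on the absence of strong interaction, and antagonism pulls the marginal effects towards null. A check that starts only after two non-neutral margins can therefore stay off where the margins mislead most.

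Two analysts could apply this text differently, and settling the matter after unblinding would be post hoc.

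**Working it through.** **1. Reproduce the planning figures.** Inputs from Section 2.6: 35% against 26%, 85% power; "468 patients per group are required" and "500 patients per group (1000 total) are planned". From Section 3.1: "All statistical significance tests will be two‐sided, with a significance level of 5" per cent.

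- Mortality, arcsine formula: n = 2(1.960 + 1.036)² / h², with h = 2·arcsin√0.35 − 2·arcsin√0.26 ≈ 0.196. This gives 468 per group, as stated (469 with the pooled-variance formula).
- Days: 2 × 2(1.960 + 1.282)² × 7² / 1.5² gives 916 in total, against 920 stated; power at 460 per group is 90.1%.

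The stated sizes therefore rest on 9 points and 1.5 days.

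**2. Can 5.6 be recovered?**

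- 35% − 26% = 9.0 points; 0.25 × 35% = 8.75 points.
- Reading 35% as the pooled rate gives 40% against 30%, or 10 points.
- 5.6 points is a 16% relative reduction from 35% (5.6/35), or a 25% reduction from a control risk of 22.4% (5.6/0.25). The plan states neither.
- An effect of 35% to 29.4% would need about 1249 per group for 85% power; with 500 per group the power is 47%.

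**3. Days.** 5.6% of the 9.8-day mean is 0.55 days; 5.6% of 30 days is 1.68 days. Neither is the planning effect of 1.5 days, and no base is named.

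**4. Does the size criterion bind?** Any pair of interventions has 1000/4 = 250 patients per cell. Take the interaction as the difference between two risk differences, with a normal approximation.

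- SE = √(4p(1 − p)/250). At p = 30.5%: √(4 × 0.305 × 0.695/250) = 5.82 points.
- p < 0.01 needs 2.576 × 5.82 = 15.0 points (14.6 at 28% mortality, 15.5 at 35%). Defined as half that contrast, it needs 7.5 points, still above 5.6.
- Power at p < 0.01 is about 5% for a 5.6-point interaction and 15% for 9 points.
- Days at SD 7: SE = 7√(4/250) = 0.885, so p < 0.01 needs 2.28 days, which is above 1.5 and above both conversions in step 3.
- Serious adverse events: 2.576√(4p(1 − p)/250) falls below 5.6 points once the event rate is below about 3%. At 2% it is 4.6 points, so the cutoff can bind there.

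**5. What the condition does under antagonism.** Illustrative cells: neither 35%, one alone 26%, the other alone 26%, both 35%.

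- Each margin is (35 + 26)/2 = 30.5% against 30.5%, so both marginal effects are null.
- Interaction: 35 − 26 − 26 + 35 = 18 points. SE = √[(2 × 0.35 × 0.65 + 2 × 0.26 × 0.74)/250] = 5.80 points. Power at p < 0.01 without the condition: Φ(18/5.80 − 2.576) ≈ 70%.
- The condition needs at least two of four interventions to be non-neutral. With all four margins null and tests independent: 1 − 0.95⁴ − 4 × 0.05 × 0.95³ = 1.4%.
- If one of the other two interventions has 90% power, it is met in about 13% of trials. If both have 85% to 90% power, it is met in about 75% to 83%.

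A milder case: 35%, 26.25%, 26.25%, 26.25%, where the two benefits do not add. Power for each margin falls from 85% to 33%. The interaction is 8.75 points, with only about 15% power at p < 0.01.

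**The case against.** The strongest reply is that little depends on this. Section 2.6 says the trial is not powered for interactions and that these analyses are hypothesis-generating. Section 3.1 reports the overall estimates even when an interaction is found, so no primary estimate, test or error rate changes. The 5.6-point cutoff is more permissive than 9, and because p < 0.01 already requires about 15 points, correcting the number alone would rarely change a mortality classification. All of this stands and limits the severity. It does not make the attribution in Section 3.5 correct, nor does it supply a rule for days.

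A reader might infer that the plan looks for interactions only after two positive results and so will almost never detect antagonism. The document does not support that. Neither Section 3.1 nor Section 4.2 says only; Section 3.5 is unconditional; and Section 4.4 promises stratified results without a condition. Section 3.5 can be read as the standing check, with Section 3.1 adding further terms. The condition also counts any two of the four interventions, so it can be met by interventions outside the antagonistic pair. The full-cancellation example is extreme, and for milder interactions removing the condition would seldom change what is flagged.

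A reader might also infer that the size cutoff never matters. That holds for mortality and days on the scales used above, but not for serious adverse events with rates below about 3%.

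**Conclusion.** The point holds at moderate severity.

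- **Firm:** Section 3.5 misstates the origin of its threshold (5.6 points, against 9 or 8.75 points and 1.5 days in Section 2.6). The figure cannot be applied to days, and the plan gives no conversion from the ratio-scale interaction term of the mortality model to an absolute effect.
- **Firm as an inconsistency:** Sections 3.1 and 4.2 attach a condition that Section 3.5 lacks.
- **Conditional:** if that condition governs, an 18-point antagonistic interaction with about 70% power would be examined in about 1.4% of trials when all four margins are null, and more often when the other interventions work.

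The figures assume 250 per cell, mortality near 30%, the plan's SD of 7 days, normal approximations and independent main-effect tests. The cell risks are illustrative. It is not a must-fix, because the analyses are exploratory and the overall results are reported regardless.

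**What to change.** 1. Remove the condition on more than one non-neutral intervention from Sections 3.1 and 4.2, so that Section 3.5 applies whatever the main results show.
2. In Sections 3.1, 3.5 and 4.4, replace 5.6% by the actual planning effects: 9 (or 8.75) percentage points on the risk-difference scale for 90-day mortality, and 1.5 days for days alive outside hospital. Give a separately justified value for serious adverse events. Alternatively, keep 5.6% for the risk outcomes with its own justification, drop the claim that it is the planning effect, and still state a cutoff in days.
3. Name the scale on which the interaction is judged and how it is obtained from the log-binomial or logistic model. Name the regression model for days; the linear model already listed as a sensitivity analysis in Section 3.2.2 is one candidate.
4. Report pairwise interaction estimates with 95% confidence intervals, labelled exploratory.

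The cost is SAP wording and a few extra tables. The downside is a few more exploratory estimates to interpret with care. Sample size and primary analyses are untouched.
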